## Discussion

Despite the evidence that interventions based on SDT and MI are effective in increasing White individuals’ physical activity, the combined efficacy of SDT and MI interventions on physical activity within minority groups has yet to be examined. The current study will determine whether SDT and MI-based interventions can be used to decrease the racial/ethnic disparity in physical activity.

This study has a number of strengths. A carefully designed, clinically- and theory-driven intervention will be used. Additionally, a rigorous treatment fidelity assessment will be conducted to determine the extent to which the exercise instructors followed the research protocol and utilized MI and SDT techniques during the intervention, the effect of the intervention exercise, and ways to improve the quality of future studies.

The current study also has limitations. The primary outcome in this study is level of physical activity, which will be assessed using a self-report measure (i.e., the IPAQ) rather than an objective measure of activity. This method was chosen because the IPAQ is a valid measure to assess individuals’ overall level of physical activity [63]. Future studies should utilize self-report measures, as well as objective measures of activity. Another study limitation stems from the fact that the racial/ethnic composition of the exercise instructors in this study does not match the racial/ethnic composition of the sample. Research suggests that, “A culturally centered intervention must consider the role of ethnic and racial similarities and differences in the client–therapist dyad. This dimension brings into focus the consideration of ethnic and race matching in the client–therapist dyad, as it may be important to acknowledge ethnic, racial, or cultural similarities and differences.” [70, 71]. Unfortunately, only White instructors are available to teach at the Southwest Syracuse YMCA and the Downtown Syracuse YMCA during the course of the intervention, and certain classes that are predominantly composed of minorities will not be taught by an instructor who is a racial/ethnic minority.

Given the Public Health concern posed by the fact that minorities are at an increased risk of becoming obese and developing chronic diseases associated with inactivity, this study will examine whether this type of intervention could cause a meaningful increase in motivation in this population, as well as a corresponding change in level of physical activity [72]. Additionally, this research should motivate future studies to examine whether interventions based on SDT and MI can motivate minority populations to engage in and maintain other positive health behaviors, such as utilizing preventative medicine or making healthier dietary choices.

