## Abstract

**Background:**

Although the mental and physical benefits of physical activity are well-established, there is a racial/ethnic disparity in activity such that minorities are much less likely to engage in physical activity than are White individuals. Research suggests that a lack of motivation may be an important barrier to physical activity for racial/ethnic minorities. Therefore, interventions that increase participants’ motivation may be especially useful in promoting physical activity within these groups. Physical activity interventions that utilized the clinical technique of motivational interviewing (MI) in conjunction with the theoretical background of self-determination theory (SDT) have been effective in increasing White individuals’ physical activity. Nevertheless, it remains unclear the extent to which these results apply to minority populations.

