### Hypotheses for the primary outcome: physical activity

*Hypothesis 1A*: White participants will report engaging in more physical activity than participants from minority groups at baseline (i.e., a significant main effect of race/ethnicity).
*Hypothesis 1B*: There will be a greater increase in physical activity from baseline among the intervention groups than among the control groups (i.e., a significant main effect of condition).
*Hypothesis 1C*: There will be a greater increase in physical activity from baseline for minority participants in the intervention groups than White participants in the intervention groups (i.e., a significant race/ethnicity by condition interaction).
*Hypothesis 1D*: Participants in the intervention groups will experience a greater increase in need fulfillment during exercise (i.e., autonomy, competence, relatedness and intrinsic motivation) which will mediate the effect on physical activity.$$ Condition\to Need\  Fulfillment\to Physical\  Activity $$

*Hypothesis 1E*: Participants in the intervention condition will report that their instructor utilizes MI skills more frequently which will mediate the effect on physical activity.$$ Condition\to Instructor\hbox{'}s\  Perceived\  use\  of\ MI\  Skills\to Physical\  Activity $$

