### Hypotheses for secondary outcomes: need fulfillment, well-being, adherence

*Hypothesis 2A*. Participants in the intervention groups will experience a greater increase in need fulfillment, psychological well-being, and physical activity adherence than participants in the control groups (i.e., a significant main effect of condition).

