### Participants

An a priori ANOVA power analysis was conducted to determine how large a sample would be needed to detect significant main effects and interactions (G*Power version 3.1.3., 2010). This was estimated using a large effect size (f = 0.50), an alpha level of 0.05, and the power was estimated at 0.80. This power analysis determined that 48 participants are needed in the sample in order to detect a statistically significant change in an effect of this size.

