### Planned statistical analyses

The analysis plan involves a 2 (race/ethnicity) × 2 (condition: intervention vs. control) factorial ANCOVA with pretest scores entered as covariates to test Hypotheses 1A-1C involving physical activity (assessed by the International Physical Activity Questionnaire [63]). Analysis of variance will be used to test Hypothesis 2A involving need fulfillment (assessed by the Basic Psychological Needs in Exercise Scale [65] and the Behavioural Regulation in Exercise Questionnaire [66]), physical activity adherence (assessed by how often participants attend the YMCA six months post-intervention), and psychological well-being (assessed by the Psychological General Well-being Index [64]). When examining whether mediators account for the relationship between intervention condition and physical activity, the Preacher and Hayes [69] nonparametric bootstrap approach will be used (i.e., Hypothesis 1D using the Basic Psychological Needs in Exercise Scale [65] and the Behavioural Regulation in Exercise Questionnaire [66] and Hypothesis 1E assessed by the Client Evaluation of Motivational Interviewing Scale [60]).

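### The Discussion asks whether motivation rises in minority participants, but motivation and need fulfillment are planned only as whole-sample comparisons, so no stated test addresses that question

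*Protocol article*

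**What the plan says.** - **The question.** The Abstract gives as motivation that "it remains unclear the extent to which these results apply to minority populations". The closing paragraph of the Discussion, whose subject is minorities, says the study will "examine whether this type of intervention could cause a meaningful increase in motivation in this population", together with a corresponding change in activity.
- **Motivation and need fulfillment.** Hypothesis 2A predicts a greater increase in the intervention groups "than participants in the control groups (i.e., a significant main effect of condition"). Under Planned statistical analyses, "Analysis of variance will be used to test Hypothesis 2A involving need fulfillment", and the same method covers adherence and well-being. No race/ethnicity factor is named.
- **Mediation.** Hypotheses 1D and 1E are single paths from condition through the mediator to physical activity, tested by bootstrap. No race/ethnicity moderator is named.
- **Physical activity.** Race/ethnicity enters only here, in a 2 x 2 ANCOVA of the IPAQ with pretest as covariate. Hypothesis 1B is the condition main effect: "There will be a greater increase in physical activity from baseline among the intervention groups than among the control groups". Hypothesis 1C is the race/ethnicity by condition interaction, predicting a larger gain in minorities.
- **Randomization.** Assignment to condition was stratified by minority status within site.

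**The concern.** A condition main effect over everyone answers whether the intervention works on average in this mixed sample. It does not answer whether motivation rises in minority participants, because the average can be positive when only White participants benefit. The article itself says earlier evidence for combined SDT and MI interventions comes from primarily White samples, so a benefit in White participants that is not shown in minorities is a pattern this trial should be able to expose.

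The gap is clearest for motivation and need fulfillment. The Discussion names motivation in minorities as something the study will examine, yet neither Hypothesis 2A nor Hypotheses 1D and 1E, as written, involve race/ethnicity. At stake is whether the closing statement will have a result behind it.

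**Working it through.** **Inputs**
- Participants section: "This was estimated using a large effect size (f = 0.50"), alpha 0.05, power 0.80, N = 48. For two equal groups, d = 2f = 1.0.
- Table 1: White 15 intervention and 16 control. Minority 9 + 3 + 0 = 12 intervention and 11 + 1 + 2 = 14 control, counting Other as minority (an assumption). White share 31/57 = 54.4%.
- Assumptions: outcome SD 1, normal errors, no covariate gain, no dropout, no class clustering, two-sided 0.05.

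**1. The plan's own figure.** Noncentral F power with λ = f²N = 0.25 × 48 = 12, four groups and 3 numerator df gives 0.803, so 48 is reproduced. The calculation is for the whole sample, and no figure is given for minorities.

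**2. Pooled test when the effect exists only in White participants.** With effect d in White participants and 0 in minorities:
- Expected arm difference = (15/27)d = 0.556d.
- The mixture adds variance (15 × 12/27²)d² = 0.247d² in the intervention arm. Residual variance is about 1 + (27 × 0.247/55)d² = 1 + 0.121d².
- SE = √(1/27 + 1/30) × residual SD = 0.265 × residual SD.
- d = 1.0: 0.556/(0.265 × 1.059) = 1.98. With 55 df (critical value 2.004), power is 0.49.
- d = 0.8: 0.444/(0.265 × 1.038) = 1.61, and power is 0.35.

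A simulation of 20,000 trials with the same cells gives 49.2% and 35.1%. At d = 0.5 it gives 16.5%.

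**3. The 2 x 2 model, as planned for the IPAQ (no covariate here).** In the same scenario:
- Main effect: expected value d/2, SE = ½√(1/15 + 1/16 + 1/12 + 1/14) = 0.266. At d = 1.0 the ratio is 1.88.
- Interaction: expected value d, SE 0.533. The ratio is again 1.88.
- Both therefore have power of about 0.45 (53 df). At d = 0.8 both are about 0.31.
- By simulation, 1B is significant with 1C not significant in 26% of all trials at d = 1.0 and 22% at d = 0.8.
- 1B and 1C both significant in the hypothesised directions: under 0.1% of trials at d = 0.5, 0.8 and 1.0.

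**4. What a minority contrast would deliver.** SE = √(1/12 + 1/14) = 0.393. The 95% half-width from the 2 x 2 model is 2.006 × 0.393 = 0.79 SD. Power from a separate comparison of 12 with 14 is as follows.

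| True d | Minority, 12 vs 14 | Whole sample, 27 vs 30, same d in everyone |
|---|---|---|
| 1.0 | 0.68 | 0.96 |
| 0.8 | 0.50 | 0.84 |
| 0.5 | 0.23 | 0.46 |

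Power of 0.80 at d = 1.0 would need 17 per arm, or 34 minority participants against the 26 enrolled.

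**The case against.** **The pooled tests match pooled hypotheses.** Hypothesis 1B is stated for all participants and tested that way, which is no error. This stands, and 1B is not part of the point.

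**For physical activity, race/ethnicity is tested.** The Discussion's aim of reducing the racial/ethnic disparity in activity is a difference in effects, which is what 1C tests. The minority effect equals the unweighted average effect plus half the minority-minus-White difference, so 1B and 1C both positive as hypothesised imply a positive minority estimate. With a White-only effect that combination almost never occurs (step 3). This stands for the IPAQ. The limit is that 1C asks whether effects differ, not how large the minority effect is, and a non-significant 1C settles neither. It does not cover motivation, need fulfillment or well-being.

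**The 49% is not a false-positive rate.** A reader might set it against 5% and infer a type I error inflated several-fold. The documents do not support that. In this scenario the pooled null is false, so rejecting it is correct. The White-only scenario is also the reviewer's, since the protocol does not assign f = 0.50 to one stratum.

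**Nothing says pooled results will be reported as minority results.** That is correct. A reader might infer it from the Discussion, but no section states it.

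**The article is condensed.** The ANOVA for 2A is named without its factors, and a fuller plan may include race/ethnicity. That is possible. But the article itself words 2A as a condition main effect and sets the minority question for motivation, so the mismatch lies between two things it does state.

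**Conclusion.** The point holds in a limited form. The Discussion commits the study to examining motivation in minority participants, and no stated hypothesis or analysis tests this. Motivation and need fulfillment appear only in a whole-sample condition effect and in mediation paths without a race/ethnicity term. If the benefit were confined to White participants, the pooled 2A-type test would be significant in about 49% (d = 1.0) or 35% (d = 0.8) of trials, and nothing else stated for those outcomes would show that minorities had not gained. The percentages rest on the Table 1 cells and the assumptions listed above. Other assumptions would move the figures but not the direction.

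This is an inexpensive improvement to secondary and mediation analyses. It is not a defect in the primary test.

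**What to change.** Under Planned statistical analyses:
- Use the 2 (race/ethnicity) x 2 (condition) model for the need fulfillment, motivation and well-being outcomes, as already planned for the IPAQ, with the pretest as covariate where there is one.
- From each model, including the IPAQ model, report the condition effect within minority and within White participants with 95% CIs, labelled as secondary contrasts.
- State that any conclusion about minorities rests on the minority contrast, not on the pooled main effect or on a non-significant interaction.

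Alternatively, reword the closing paragraph of the Discussion so that its statement on motivation refers to the whole sample.

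**Cost.** One added term and two contrasts per model, with no new data, because minority status is already a stratification factor. The downside is precision: with 12 against 14 the minority interval is about ±0.79 SD without a covariate, so even a sizeable true effect may not be distinguishable from zero. The report should say so.
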